## 2.3 SAMPLE SIZE

Specifying a formal sample size target is not possible as this is an opportunistic retrospective analysis of antibiotic prescription data provided by our partners Rx Info Ltd, Public Health England (PHE) and Public Health Wales (PHW). Data will be available for around 100-120 English NHS Trusts and around 15-20 Welsh NHS hospitals, with up to 19 weekly data points for each.

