# 3. STATISTICAL PRINCIPLES

## 3.1 LEVELS OF CONFIDENCE AND P-VALUES

All hypothesis tests and confidence intervals (CIs) will be two-sided. We will use a 5% significance level and present 95% CIs.

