#### 5.1.2 TIMING, UNITS AND DERIVATION OF PRIMARY

Aggregated weekly antibiotic usage data (total dispensing to hospital locations) will be collected from Rx Info Ltd (and provided via PHE and PHW), and weekly patient activity data will come directly from PHE and PHW. As a consequence of the extraction and aggregation methods differing between PHE and PHW (as described in separate documents), English and Welsh data will be analysed separately.

Date of introduction of PCT testing, or not, and whether a Trust that did not introduce PCT testing between March and June 2020 was using it already or not, will be collected via direct contact with hospitals in WP 1.1. For the Trusts introducing PCT testing, their first week of PCT use will be defined as the ISO week following the reported introduction date.

The three different data elements (antibiotic usage, patient activity, PCT usage) will be merged to create a single analysis dataset; this will be done by matching their NHS Organisational Data Service (ODS) codes.

tDDDs are defined as all ATC J01, J04AB02 (rifampicin), A07AA12 (fidaxomicin) and A07AA09 (vancomycin – oral).

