## 5.2 ANALYSIS METHODS

### 5.2.1 LIST OF METHODS AND PRESENTATION

A controlled interrupted time series (ITS) will be undertaken with variable dates of introduction of PCT testing across Trusts (McLintock et al. 2014; Kontopantelis et al. 2015; Bernal et al. 2017, 2018; Bottomley et al. 2019; Bell et al. 2021).

We will fit a linear mixed effects model with ISO week, use of PCT testing (yes/no) in ICU in each ISO week, use of PCT testing (yes/no) in ED/acute wards in each ISO week, and their interaction with ISO week as independent fixed-effect variables, and Trust as a random-effect variable. Based on this ‘segmented’ regression model, we will estimate the level and trend of the rate of antibiotic usage before and after the introduction of PCT testing and test the null hypotheses that 1) the level (i.e. model intercept) and 2) the trend (i.e. model slope) do not change following the introduction of PCT testing.

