### 5.2.4 ALTERNATIVE METHODS IF DISTRIBUTIONAL ASSUMPTIONS NOT MET

If the data show signs of autoregression, we will add a first-order autocorrelation and/or moving average covariance structure to the model.

If the trend over time in the data is distinctly non-linear, we will add additional terms (e.g. quadratic ISO week) to the regression model.

If appropriate, we will consider more complex random effects such as Trust-specific slopes in addition to Trust-specific intercepts.

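### The primary model has only a random Trust intercept and no rule for adding Trust slopes, so the PCT level test and especially the trend test may be anti-conservative if Trust trends differ

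*SAP*

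**What the plan says.** SAP 5.2.1 regresses the weekly antibiotic rate on ISO week, a weekly indicator of PCT use in ICU, a weekly indicator of PCT use in ED/acute wards, and the interaction of each indicator with week, with "Trust as a random-effect variable". Two null hypotheses are tested: no change in level and no change in trend after PCT is introduced.

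Section 5.2.4 makes clear that the random effect is an intercept, because slopes would come on top of it: "If appropriate, we will consider more complex random effects such as Trust-specific slopes in addition to Trust-specific intercepts". It treats autocorrelation more firmly: "If the data show signs of autoregression, we will add a first-order autocorrelation and/or moving average covariance structure to the model". Section 5.2.3 plans residual plots, (partial) autocorrelation functions, Durbin-Watson tests and standard regression diagnostics. None of these is aimed at differences in slope between Trusts. Random slopes are not among the sensitivity analyses in 5.2.5, and robust standard errors are not mentioned.

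On inference, 3.1 states: "All hypothesis tests and confidence intervals (CIs) will be two-sided" and "We will use a 5% significance level and present 95% CIs". On size, 2.3 states: "Data will be available for around 100-120 English NHS Trusts and around 15-20 Welsh NHS hospitals, with up to 19 weekly data points for each". Section 5.1.2 adds that "English and Welsh data will be analysed separately".

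**The concern.** One of the two tested quantities is a slope. Section 4.5.2 distinguishes never-users, always-users and adopters. In the 5.2.1 model an always-user has its PCT indicator at 1 in every week and a never-user has it at 0 in every week. Part of the PCT-by-week estimate is therefore a comparison of weekly trends between different Trusts. The right yardstick for that comparison includes the natural spread of trends between Trusts, which a random-intercept model sets to zero. Any real spread is then treated as independent weekly noise, and the model credits each Trust's 19 weeks with more information about trend than they hold.

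At stake are false-positive PCT effects and confidence intervals that are too narrow on the primary outcome. There is also a prespecification issue: whether to add slopes changes the standard errors of the primary tests, yet the SAP leaves that choice until after the data have been seen, with no rule.

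**Working it through.** **No figure to reproduce.** Section 2.3 declines a target ("Specifying a formal sample size target is not possible as this is an opportunistic retrospective analysis of antibiotic prescription data"), and the SAP states no slope variance, residual SD, autocorrelation or share of Trusts in each exposure group. Everything below is a scenario, not an estimate for this study.

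**Inputs from the SAP.** Two-sided 5% (3.1); about 100-120 English Trusts, taken as 110; about 15-20 Welsh hospitals, taken as 18; 19 weeks (2.3); the 5.2.1 model.

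**Assumptions not in the SAP.** ICU never/always/adopter 35/35/30%; ED 60/10/30%; adoption uniform over weeks 11-22; intercept SD = residual SD = 1; slope SD τ from 0 to 0.10 residual SD per week; lag-1 correlation ρ from 0 to 0.4; no PCT effect. Over the 18 weekly steps, a Trust one SD from the average trend drifts by 18τ: 0.36, 0.9 and 1.8 residual SDs for τ = 0.02, 0.05 and 0.10.

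**Step 1: hand check for a pure always-user versus never-user trend comparison (ρ = 0).**
- Sum of squares of centred weeks: S = 19 × (19² − 1)/12 = 570.
- True variance of one Trust's fitted slope: 1/S + τ².
- Variance the random-intercept model reports, with its residual variance inflated by the ignored slopes: (1 + τ²S/18)/S.
- SE ratio r = √(reported/true); type I error = 2[1 − Φ(1.96r)].

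| τ | reported | true | r | type I error |
|---|---|---|---|---|
| 0.02 | 0.001777 | 0.002154 | 0.91 | 7.5% |
| 0.05 | 0.001893 | 0.004254 | 0.67 | 19% |
| 0.10 | 0.002310 | 0.011754 | 0.44 | 38% |

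Adopters also contribute a within-Trust comparison, so the full model should be affected somewhat less.

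**Step 2: simulation of the full 5.2.1 model, 110 Trusts, 300 replicates, two-sided z test.** Each cell gives the range over the ICU and ED terms, level / trend.

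| τ, ρ | Intercept only | Intercept + AR(1) | Intercept + slope + AR(1) |
|---|---|---|---|
| 0, 0 | 4% / 5-6% | 3-4% / 5-6% | 3-4% / 4-5% |
| 0.02, 0 | 4% / 7-8% | 4% / 6% | 3-4% / 5-6% |
| 0.05, 0 | 10-11% / 16-17% | 7-9% / 14-15% | 3-5% / 5-6% |
| 0.10, 0 | 19-26% / 32-33% | 11-13% / 24% | 3-4% / 5-6% |
| 0, 0.2 | 7% / 9-10% | 3-4% / 5% | 3-4% / 4-5% |
| 0, 0.4 | 14% / 17-18% | 4% / 4-5% | 4% / 4-5% |
| 0.05, 0.3 | 15-16% / 24-25% | 5-6% / 10-11% | 3-4% / 5-6% |

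For the intercept-only trend test, mean SE over empirical SD was 0.92-0.95, 0.71-0.73 and 0.49-0.50 at τ = 0.02, 0.05 and 0.10 (ρ = 0), in line with Step 1. Monte Carlo error is about ±2.5 points near 5% and about ±5 points near 33%.

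A second simulation at 110 Trusts and ρ = 0, also under an assumed exposure mix, gave 12% / 19% at τ = 0.05 and 26% / 35% at τ = 0.10 for intercept only, against 4-7% with Trust-clustered standard errors.

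**Step 3: Wales, 18 hospitals, 400 replicates.** At τ = 0.05, ρ = 0, intercept only gives 11-12% (level) and 16-17% (trend), much as in England. The slope + AR(1) model gives 6-8% and 5-8% over all scenarios, a slight excess for a z test on few clusters. Uncorrected sandwich errors rejected 9-14% at this size.

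**Step 4: would the autocorrelation check fire?** Approximate power = Φ(ρ√(18N) − 1.96). At ρ = 0.1 it is at least 0.99 for 100-120 Trusts and 0.38-0.48 for 15-20 hospitals. At ρ = 0.2 it is 0.91-0.97 for 15-20 hospitals.

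**The case against.** The strongest reply is that the SAP already deals with within-Trust dependence. Autocorrelation will be checked, and the remedy is a commitment rather than an option. This stands: with no slope variation, adding AR(1) brings error back to 3-5% for ρ = 0.2 to 0.4, and in England material autocorrelation would hardly be missed. A reader might infer that the SAP neglects serial correlation, and the documents do not support that. What remains is that AR(1) does not stand in for differing trends. Even if ignored slopes show up in the residual autocorrelations and trigger the step, the trend test stays at 14-15% or 24% in the ρ = 0 scenarios.

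A second reply is that the standard errors may be perfectly sound. This also stands as a limit. A reader might infer that the planned standard errors are too small as a matter of fact, but the SAP holds no variance data to show it. With no slope variation the planned model rejects at 4-6%, and at a slope SD of 0.02 residual SD at 4-8%.

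A third tempting inference is that the inflation is worse in Wales. The simulated inflation is about the same. The Welsh problem is narrower: low autocorrelation may go undetected, and inference rests on few clusters.

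Finally, the SAP does mention Trust slopes. It does so without a criterion, a deciding step or a matching diagnostic, so it does not fix what will be done.

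**Conclusion.** The point holds in conditional form. The default primary model omits Trust-specific slopes, and nothing in the SAP determines when they would be added. If Trusts differ in weekly trend by 0.05 to 0.10 residual SD per week, with 110 Trusts and no autocorrelation, nominal 5% tests reject at about 10-26% for level and 16-35% for trend. With AR(1) added, the trend test still rejects at about 14-24%. Trend is affected more than level. These sizes depend on the assumed exposure mix, adoption timing and variances, none of which the SAP states. The gap in prespecification does not depend on them. The matter should be settled before analysis; it does not invalidate the design.

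**What to change.** In 5.2.1, make a random Trust-specific week slope, alongside the random intercept, the default for the primary model, and remove the discretionary sentence on slopes from 5.2.4. Keep the planned AR/MA step, or fit AR(1) by default; the latter matters mainly for Wales. State a fallback: if the slope model does not converge, drop the slope and base tests and confidence intervals on Trust-clustered robust standard errors.

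For Wales, specify small-sample-corrected inference with cluster-based degrees of freedom, because uncorrected sandwich errors are themselves anti-conservative with 15-20 hospitals.

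The cost is SAP wording, a change to the random-effects term in the nlme package already named in 5.6, a separate inference step for the fallback and for Wales, and somewhat wider confidence intervals. Where slopes do not vary, the fuller model stayed near nominal at 110 Trusts, at 3-5%.

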### 5.2.5 SENSITIVITY ANALYSES

In addition to the 'step change' assumed for the Trusts introducing PCT testing (i.e. assuming an instant change in practice following the introduction) in the primary analysis we will also model a more gradual 'phase-in' e.g. over a four-week period.

We will consider adjusting for hospital occupancy (i.e. bed days divided by capacity) by including it as a covariate in the analysis model.

### 5.2.6 SUBGROUP ANALYSES

The outcomes defined in section 5.1 will be further subclassified, allowing us to analyse weekly trend of:

- number of DDDs of antibiotics by classification (broad spectrum, narrow spectrum)
- number of DDDs of antibiotics by route (IV, oral)
- number of DDDs of antibiotics by WHO 'AWaRe' category (Access, Watch, Reserve)
- number of DDDs of antibiotics by individual agent (in the list of CAPs, see 5.1.2)

per

- number of COVID-positive admissions
- total number of admissions
- number of COVID-positive patient bed days
- total number of patient bed days

Additionally, COVID-positive admissions and patient bed days will be further split into:

- admitted COVID-positive (<14 days pre-admission) or COVID-positive ≤day 7 post-admission)
- COVID-positive >day 7 post-admission

Furthermore, we will perform a separate analysis including critical care patients only.

### 5.3 MISSING DATA

Patterns of missingness will be explored and summarised descriptively.

### 5.4 ADDITIONAL ANALYSES

To assess the effects of introducing PCT in the ICU and ED/acute wards on antibiotic usage separately, we will fit an ITS model in which we replace the categorical variable describing the level of PCT testing (none, partial, full) with two separate binary variables indicating whether PCT was used or introduced in the ICU and ED/acute wards, respectively.

### 5.5 HARMS

Not applicable.

### 5.6 STATISTICAL SOFTWARE

All analyses will be performed in R version 4.0.0 or higher, with add-on packages such as ‘car’ for time series functions, ‘nlme’ for mixed effects models, and ‘ggplot2’ for graphics.

6.2 DATA MANAGEMENT PLAN

6.3 STUDY MASTER FILE AND STATISTICAL MASTER FILE

6.4 OTHER SOPS OR GUIDANCE DOCUMENTS

## SAP DEVIATION LOG

|                       |  |                   |  |
|-----------------------|--|-------------------|--|
| Document number:      |  | Document version: |  |
| Reason for deviation: |  |                   |  |
|                       |  |                   |  |
